## Abstract

**Background:**

Ankle sprains and fractures are most common injuries in orthopedic and trauma surgery. The concurrent occurrence of syndesmosis ruptures in these injuries represents a more complex problem, as they often remain undetected.

A proper and accurate treatment of injuries of the syndesmosis, both isolated and combined with fractures, is necessary to avoid long-term consequences (chronic instability, cartilage damage, and post-traumatic osteoarthritis). The most popular treatment option is a static screw fixation and the newly developed dynamic TightRope® (Arthrex, Naples, FL, USA).

The aim of this pilot study is to compare monitor ankle range of motion and maximum ankle power in gait as functional outcome parameters of instrumented gait analysis, as well as clinical and radiographic outcome for assessing the stabilization of acute syndesmosis rupture with either a static implant (a 3.5 mm metallic screw) or a dynamic device (TightRope®).

**Methods:**

This prospective, randomized, controlled, clinical trial will be carried out at the Center for Orthopedics, Trauma Surgery and Spinal Cord Injury of the University Hospital Heidelberg. Adult patients, who suffer from an acute syndesmosis rupture, both isolated and in combination with fractures of the lateral malleolus (Weber C and Maisonneuve fractures) and who are undergoing surgery at our trauma center will be included in our study. The patients will be randomized to the different treatment options (screw fixation or “TightRope®”). Subsequent to the surgical treatment, all patients will receive the same standardized follow-up procedures including a gait analysis and MRI of the ankle at 6 months follow-up.

The primary endpoint of the study is the successful healing of the syndesmosis and biomechanical investigation with gait analysis.

**Discussion:**

The results of the gait analysis from the current study will help to impartially and reliably evaluate the clinical and biomechanical outcome of both treatment options of acute syndesmosis ruptures. We hypothesize that the dynamic fixation provides an equivalent or better biomechanical, clinical, and radiographic outcome in comparison to the screw fixation.

**Trial registration:**

German Clinical Trials Register (DRKS) DRKS00013562. Registered on July, 12, 2017.

## Background

Ankle fractures are common injuries in the clinic and operative daily routine of a trauma surgeon [1]. Syndesmosis ruptures occur in 13% of these fractures and represent a more complex problem [2]. The syndesmosis ligament connects the tibia and the fibula above the ankle joint. It is, among other ligaments, responsible for its stabilization. Isolated injuries of the syndesmosis are extremely rare and often remain undetected in the clinical routine [3]. There are several clinical tests (Frick test, squeeze test, cross-leg test, fibula translation test) which confirm the suspicion of injury, but cannot secure it. Although certain syndesmotic injuries may be diagnosed radiographically, these injuries are often missed because of the inability of radiographs to detect them. Tibiofibular clear space greater than 6 mm (diastasis) in AP X-ray view is considered as a radiologic criterion for instability.

Today, magnetic resonance imaging (MRI) is the “gold standard” for the pretherapeutic evaluation of syndesmotic injury with a sensitivity of 100% and a specificity of 93% [4].

A proper treatment of injuries of the syndesmosis complex is challenging but necessary to avoid malreduction of the syndesmosis that alters tibiofibular joint kinematics and leads to chronic instability, cartilage damage, and early osteoarthritic changes of the ankle joint [5, 6]. Therefore, accuracy and maintenance of reduction of the syndesmosis are considered essential when treating ankle fractures with concomitant syndesmosis injury.

Even small joint gaps, axis deviations, or instabilities lead to considerable dysfunctions and thus increase the risk of post-traumatic arthrosis development [7].

The most popular treatment option of the unstable distal tibiofibular joint is a static 3.5-mm screw fixation (FA DePuy Synthes, USA) with one or multiple screws through three or four cortices. Disadvantages of the syndesmosis screws are partial weight-bearing for at least 6 weeks, neglect of the dynamic property of the syndesmosis, and an increased risk of chronic instability as well as the potential of late diastasis due to loosening, screw breakage, or screw removal. Furthermore, syndesmosis malreduction is reported to occur in up to 50% with syndesmotic screw fixation [8, 9]. Six to 8 weeks after the initial treatment, a mandatory implant removal is required to begin weight-bearing at our trauma center. In contrast, some authors prefer to retain the syndesmotic screw in place until she breaks. Whether or not the syndesmotic screw should be removed prior to weight-bearing is still discussed [10].

In contrast to screw fixation, the flexible, dynamic TightRope® (Arthrex, Naples, FL, USA) suture button device was developed for physiological stabilization of the distal tibia and fibula. The use of this dynamic suture button device has increased rapidly over the last years. Theoretically, this suture button device allows physiological motion of the syndesmosis without need for implant removal, which may reduce the risk of recurrent syndesmotic diastasis as described after syndesmosis screw removal [11, 12].

Biomechanical investigations have demonstrated that the strength of TightRope® device is comparable to a tricortical 3.5-mm syndesmotic screw. Several recent studies assessed syndesmosis stabilization with the suture button device and comparative studies reported equivalent or better functional results in comparison to the syndesmotic screw [3, 13–16].

Instrumented gait analysis is a well-established procedure at our trauma center, which allows objective quantification of gait deviations in the context of conservative and surgical treatment in the lower extremity. For assessment, the patient is equipped with skin-based markers and asked to walk repeatedly along a 5-10-m-long walkway at self-selected speed for monitoring joint motion via optical motion tracking. Floor mounted force plates allow for determining ground reaction forces when walking across them. This so-called “standard clinical instrumented 3D gait analysis” is a modern in vivo analysis, which allows for analyzing joint motion and joint kinetics of the major lower limb joints [17, 18].

To date, no study has yet compared both treatment options in terms of biomechanical outcome with kinetic, kinematic changes, and compensation mechanisms.

The majority of earlier studies of syndesmosis fixation, which demonstrated the equality of both treatment options, used only standardized questionnaires and plain radiographs to assess syndesmosis reduction and clinical outcome.

Therefore, the purpose of this prospective randomized controlled single-center study was to assess the functional outcome namely by ankle range of motion as well as maximum ankle power as obtained via gait analysis and to rate the clinical and radiologic outcome by monitoring the stabilization of acute syndesmosis rupture with either a static implant (a 3.5-mm metallic screw through three cortices) or a dynamic device (TightRope®).

In this study, we expect that dynamic fixation would provide an equivalent or better clinical and radiologic outcome as well as a similar or better function of the ankle, i.e., larger range of ankle motion within the gait cycle and a larger maximum plantar flexion power at pre-swing. It can be assumed that when the maximum ankle performance normalizes, there is sufficient healing.

This study focuses mainly on the treatment of syndesmosis rupture, but it also aims to gain insights into patients’ satisfaction in correlation to functional outcome and surgical technique. Additionally, the study targets to show how risk factors, different therapeutic modalities, and/or treatment strategies influence this outcome. In future, the risk of long-term consequences and complications should be minimized by analyzing the new and already existing data, the clinical-functional follow-up examination, and the subjective result.

The study protocol for this study is described in the present manuscript.

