### Randomization

Patients will be randomly assigned to one of two groups (intervention or control) using a computer-generated random block assignment in a 1:1 ratio using nQuery Advisor v7.0 software (Statsols, Cork, Ireland). This method helps in maintaining the balance of treatment assignment while reducing the potential for selection bias. Patients, researchers performing the follow-up examination, and the trial statistician will be blinded to the group allocation. If the treatment of syndesmosis rupture is not accomplished after randomization due to an intraoperatively observed missing acute syndesmosis rupture with no need of stabilization, the patient will be excluded from final analysis. At the date of screw removal 6 to 8 weeks after the operation, a blinding of the patients will no longer be possible.

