**Table 1 Tab1:**
[figure not shown]
Overview of clinical and radiologic follow-up. *CT* computed tomography, *MRI* magnetic resonance imaging, *SF-12* 12-item Short Form Health Survey, *VAS pain* visual analog scale for pain

MRI images will be assessed by a senior radiologist for degenerative changes of the tibiotalar joint and the syndesmosis structure (unaffected, hyperintense signal alteration on T2, partial tear, complete tear), widening, and calcification. By using questionnaires preoperatively and postoperatively after 6 weeks and 3, 6, and 12 months during the appointments, patients can provide information on pain, mobility of foot and ankle, and quality of life (SF-12) [19] during the course of treatment. General patient data, including age, profession, body mass index (BMI), risk factors, medication, concomitant diseases, previous surgeries, and details of the accident, will be documented preoperatively.

At 25 weeks postoperatively, patients also receive a gait analysis and MRI is performed to assess motion anomalies and the healing process of the syndesmosis.

The planned study will run over 2 years. Patients will be admitted over a period of 1 year. Each patient will be treated and followed-up over a 12-month period.

All data will be stored and monitored using pseudonyms. The data of all patients will be analyzed statistically and compared at the end of the 2 years (Table 1).

Furthermore, all data of the participating patients will be carefully assessed, and all adverse events and complications of the treatment will be reported at the end of this trial. The harms will be categorized according to their degree of severity in either serious or non-serious.

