### Sample size calculation and statistical analyses

Formal sample size determination is not possible as potential effects are not yet known. Data from previous studies were utilized to determine the necessary sample size [23–25]. We plan a sample size of 25 patients, who will be treated with the cortical screw fixation and 25 patients, who will be treated with the dynamic TightRope® system within 2 years. The patients will be randomized to the two different treatment options. The randomization will be independent of the surgeon and the doctor who will do the examinations and the questionnaires.

The Shapiro-Wilk test will be used to check if our population is normally distributed. Standard unpaired Student’s *t* test to detect significant changes between the two groups will be conducted, if they are normally distributed. In contrast, possible differences for continuous data and scores between groups will be evaluated with the Wilcoxon *U* test, if no normal distribution exists.

The empirical distribution of continuous data and scores will be reported and calculated with means, standard deviation (SD), median, minimum, and maximum values and with absolute and relative frequencies for categoric data as well as unpaired *t*-test *p* values to depict a significant difference between the different groups. All descriptive analyses will be calculated for demographic data and for the dependent variables derived from the functional assessment, gait analyses results, and questionnaires of both groups.

An independent senior statistician of the Institute of Medical Biometry and Informatics of our university will perform the analysis. The intention-to-treat population will be used.

The analysis and illustrations will be carried out by use of SPSS version 25.0 for 135 Windows (IBM Corp., Armonk, New York, USA) and GraphPad Prism version 6.00 for Windows (GraphPad Software, San Diego, California, USA). For the representation of statistical relationships, the Pearson correlation coefficient will be used. The final details of the statistical analysis will be established in a statistical analysis plan, which will be completed before the closing of the database (before the end of data collection). A *p* value of ≤ .05 will be used to indicate statistical significance. Only a complete follow-up examination will be considered in the statistical analyses.

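### The aim of showing how risk factors influence outcome is too strong for observed factors in a 50-patient pilot, and Pearson correlation is fixed without a rank alternative

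*Protocol article*

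**What the plan says.** Two subsidiary aims stand together in the Background of the protocol article. The first is modest: "it also aims to gain insights into patients’ satisfaction in correlation to functional outcome and surgical technique". The second is not: "the study targets to show how risk factors, different therapeutic modalities, and/or treatment strategies influence this outcome".

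The section on sample size and statistical analyses gives one sentence on associations: "For the representation of statistical relationships, the Pearson correlation coefficient will be used". It attaches no condition on distribution or type of variable. The same section chooses between Student's t test and a rank test for group comparisons according to a Shapiro-Wilk check, and sets one general threshold: a p "value of ≤ .05 will be used to indicate statistical significance". The planned number is 25 per arm ("We plan a sample size of 25 patients, who will be treated with the cortical screw fixation and 25 patients"), and only patients with complete follow-up are to be analysed.

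The text under Table 1 lists what is recorded before surgery: "General patient data, including age, profession, body mass index (BMI), risk factors, medication, concomitant diseases, previous surgeries, and details of the accident".

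The Objectives and hypotheses section calls the trial a pilot and adds hypothesis generation as an objective. The Primary outcome measures section repeats the pilot character. Final analysis details are left to a statistical analysis plan that is not shown.

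**The concern.** To show how a factor influences an outcome is a causal and confirmatory goal. Only the choice of fixation is randomised here. An unadjusted association between outcome and, say, BMI or a concomitant disease in a small pilot can suggest a question but cannot demonstrate an influence. The Background therefore promises more than the Objectives section claims for the trial.

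The stated method has a separate weakness. Pearson's coefficient measures linear association between numerical variables. The protocol allows that its scores may be non-normal and guards against this for group comparisons, but not for correlations.

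At stake is the reading of the subsidiary results. The Background goes on to hope that analysis of new and existing data will reduce later complications, so a weak or chance association could be given more weight than it deserves.

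**Working it through.** **1. What is randomised.** Allocation is by "computer-generated random block assignment in a 1:1 ratio" to screw or TightRope. The eight items listed under Table 1 are patient characteristics or history, so they are observed. For fixation method, a causal reading of a group comparison is available. For the other factors it is not.

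**2. Aim against status.** The Background uses a verb of demonstration for risk factors and a verb of insight for satisfaction. The Objectives section limits the tested hypotheses to the comparison of the two treatments and describes anything further as hypothesis generation. The sample size paragraph concedes that "Formal sample size determination is not possible as potential effects are not yet known". The stronger verb thus falls on the aim with the weaker design.

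**3. Pearson against the plan's own rank rule.** For group comparisons of continuous data and scores, the rule is a t test if normal and a rank test if not. For relationships, the rule is Pearson in every case. The two meet in the satisfaction aim, because surgical technique has two levels. With technique coded 0/1, the test of Pearson's r is algebraically the unpaired t test:

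t = r √(n − 2) / √(1 − r²)

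For n = 50 and r = 0.279: 0.279 × 6.928 / √(1 − 0.078) = 2.01, the two-sided 5% critical value of t on 48 degrees of freedom. So if satisfaction scores were not normal, the group rule would require the rank test while the correlation rule would return the t test on the same data. For a nominal factor with more than two categories, such as profession, Pearson's r depends on arbitrary numerical codes.

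**4. What a correlation can tell in 50 patients.** Inputs: n = 50 (25 + 25, the maximum); α = 0.05, taken as two-sided because the protocol does not say.

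- Critical value: r = t / √(n − 2 + t²) = 2.011 / √(48 + 4.043) = 0.279; r² = 0.078.
- 95% confidence interval at that r, by Fisher's z: atanh(0.279) ± 1.96/√47 = 0.287 ± 0.286, which transforms back to about 0.00 to 0.52.
- True r detectable with 80% power: tanh[(1.960 + 0.842)/√47] = tanh(0.409) = 0.39.
- Power for a true r of 0.3: Φ(0.310 × √47 − 1.960) = Φ(0.162) = 0.56.

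With 40 complete patients (an assumed loss of 10), the critical r is 0.31, the r detectable with 80% power is 0.43, and power for r = 0.3 is 0.47.

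**5. Illustration of chance findings.** The protocol gives no number of association tests, so k is an assumption. For k independent tests with no true association, the chance of at least one p ≤ .05 is 1 − 0.95^k:

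| Assumed k | Independent | Test statistics correlated 0.5 |
|---|---|---|
| 5 | 0.23 | 0.18 |
| 8 | 0.34 | 0.25 |
| 20 | 0.64 | 0.42 |

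k = 8 would correspond to the eight recorded items against a single outcome. The correlation of 0.5 is also an assumption. The right-hand column comes from numerical integration over an equicorrelated normal model.

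**The case against.** The case against is substantial, and much of it stands.

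- **Exploratory status.** A reader might infer that nothing marks these analyses as exploratory. The documents do not support that. The trial is called a pilot in several places and hypothesis generation is a stated objective. Risk factors appear in neither the tested hypotheses nor the listed outcomes. What remains is that the Background sentence is worded against that status.
- **Link between Pearson and risk factors.** A reader might infer that Pearson is prescribed for the risk-factor aim. It is not. It is named for relationships in general, and the verb used suggests description as much as testing. It is, however, the only association method given, and the neighbouring satisfaction aim speaks expressly of correlation.
- **Multiplicity.** A reader might count the missing error control as a fault. It may be in the unseen analysis plan, so its absence is not held against the protocol. The list of factors to be examined may be there too.
- **Consequence.** A reader might infer that chance associations would be reported as influences. No text says so; it is only a possibility that the wording leaves open.
- **Scope of the factors.** The recorded items are general patient data, and nothing says that each will be related to outcome. One of the treatment strategies, the fixation method, is randomised and has its own group comparison.

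Deferral to the analysis plan does not answer two things that the article itself fixes: the wording of the aim and the unconditional choice of Pearson.

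**Conclusion.** Two limited points hold. First, the aim of showing influence conflicts with the pilot, hypothesis-generating status given elsewhere, and cannot be met for factors that are only observed in at most 50 patients. Second, Pearson correlation is fixed without condition although the same section foresees non-normal scores, and the one explicit correlation aim includes a two-level factor.

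The size is small. Neither the primary endpoints, the sample size nor the screw-versus-TightRope comparison is affected. An association just reaching p ≤ .05 in the full 50 patients would explain about 8% of variance, with an interval from almost zero to about 0.52, which is an estimate for follow-up and no demonstration of influence. These figures assume two-sided testing and complete data. The family-wise figures illustrate the risk under assumed test counts and say nothing about a number planned by the sponsor.

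**What to change.** - In the Background, reword the aim: explore associations of recorded factors with outcome. Keep causal language for the randomised comparison.
- In the statistics section, or in the analysis plan before the database closes, use Spearman correlation for ordinal or non-normal scores. Pearson can stay for continuous variables with a roughly linear relation.
- For categorical factors, including surgical technique, report group differences under the existing t test or rank test rule instead of a correlation coefficient.
- Report all these analyses as exploratory estimates with 95% confidence intervals, and make no claim of significance from them.

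The cost is a few sentences, with no extra patients, visits or data. The price is that risk-factor results can be offered only as hypotheses for a later trial, which is what the Objectives section already foresees.

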## Study design/methods

### Objectives and hypotheses

The objective of this prospective randomized controlled single-center study is the comparison of gait analysis, clinical and radiographic outcome after stabilization of an acute syndesmosis rupture with either a static implant (a 3.5-mm metallic screw through three cortices) or a dynamic device (TightRope®). Due to the pilot study design, further objective is to generate additional possible hypotheses.

The following hypotheses will be tested:
H0: The biomechanical (regarding ankle range of motion and maximum plantar flexion power in the gait analysis), clinical (study questionnaire, SF-12, OMAS, VAS, FAOS), and radiological outcome is different in both treatment options.H1: The biomechanical (regarding ankle range of motion and maximum plantar flexion power in the gait analysis), clinical (study questionnaire, SF-12, OMAS, VAS, FAOS), and radiological outcome is equal in both treatment options.

Patients with acute syndesmosis rupture (isolated or combined), suitable according to the study protocol, will be randomized to the two different treatment options (screw fixation or TightRope®).

Syndesmosis reduction will be assessed using CT/3D imaging intraoperatively with ISO C 3D or CIOS Spin (Siemens Healthineers GmbH, Erlangen, Germany) as a part of our standard procedure.

Six months after the initial treatment, the patients will receive an additional gait analysis and a MRI in the follow-up examination at our outpatient clinic

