The large number of 50 patients is also remarkable. Moreover, only experienced orthopedic trauma surgeons will perform all surgical procedures which improve good external validity. The objective biomechanical outcome measurements with the aid of gait analysis are a unique characteristic which can show kinematics and functions of the ankle joint.

Limitations of the study include the diversity of ankle injury and fracture types that can bias the outcome. To minimize bias, all included patients will follow the same postoperative weight-bearing pattern.

We only perform CT/3D imaging on the fracture site. A bilateral CT investigation to detect possible anatomical variations will not be performed. A 1-year follow-up involves the danger of not being able to detect long-term complications as degenerative changes or osteolysis that could be a result of either a malreduced syndesmosis or an initially unreported osteochondral lesion. Therefore, a longer follow-up period would be interesting to observe such possible changes in the ankle mortise (widening, osteolysis, or osteoarthrosis).

Our hypothesis is that TightRope® will provide the same biomechanical, clinical, and radiological outcome with a similar or better postoperative function of the ankle in the gait analysis. Furthermore, we assume that the recovery time and the time required to return to work is shorter in the TightRope® cohort than in the static screw control group.

The results of the study should, in biomechanical terms, therefore help to demonstrate the comparability of different treatment methods by using the gait analysis as an objective and modern measurement method.

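### The stated hypotheses (H0 different, H1 equal) run opposite to the difference tests named to test them, so no test named in the protocol article can establish H1.

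*Protocol article*

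**What the plan says.** Objectives and hypotheses introduces a pair of hypotheses as those the trial will test, covering gait, clinical and radiological results. H0 ends "and radiological outcome is different in both treatment options". H1 ends "and radiological outcome is equal in both treatment options". No tolerance is attached to equality.

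Sample size calculation and statistical analyses then names the tests. For normally distributed data it is an unpaired Student's t "test to detect significant changes between the two groups will be conducted"; otherwise it is a Wilcoxon U test, also described as evaluating possible differences. Significance is p ≤ .05, and the p values are meant to depict a significant difference. The planned size is 25 per arm, and the section says that no formal calculation was possible.

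Elsewhere the expectation leans towards sameness. The abstract's discussion hypothesises that "dynamic fixation provides an equivalent or better biomechanical, clinical, and radiographic outcome". The Background says "we expect that dynamic fixation would provide an equivalent or better clinical and radiologic outcome". The Discussion expects that the suture button "will provide the same biomechanical, clinical, and radiological outcome with a similar or better postoperative function of the ankle", and says the results should help to show that the methods are comparable.

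**The concern.** H0 and H1 are oriented as in an equivalence trial, while the tests are those of a trial looking for a difference. Rejecting the null of a t test or Wilcoxon test is evidence that the arms differ, which is the protocol's H0. Failing to reject is not evidence for its H1. The stated hypotheses and the named tests therefore do not connect.

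At stake is how the result is read. Someone who takes H1 as the claim and has only these tests has one apparent route to it: treat p > .05 as support for equality. In a trial of this size, that result is common even when the arms truly differ by a moderate amount.

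**Working it through.** **1. Hypotheses against tests.** Let δ be the true between-arm difference in a continuous outcome.

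| | Null | Alternative |
|---|---|---|
| Objectives and hypotheses | δ ≠ 0 | δ = 0 |
| t test (and, in the same spirit, Wilcoxon U test) | δ = 0 | δ ≠ 0 |

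The two rows are exact reversals.

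**2. Could any test establish the stated H1?** A 5% test of the null δ ≠ 0 must reject with probability at most 5% at every non-zero δ, however small. Because power varies continuously with δ, it is then at most 5% at δ = 0 too. Exact equality cannot be shown at any sample size; a tolerance is needed.

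**3. What 25 per arm implies.** The plan gives no effect size, SD, margin or power, so there is no figure of its own to reproduce. From the documents: n = 25 per arm, 1:1, α = 0.05. Assumed: two-sided testing (the sidedness is not stated), normal data, and effects and margins in SD units, shown as a range.

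*Chance of p > .05.* Noncentral t with 48 degrees of freedom, noncentrality d·√(25/2) = 3.536·d, critical value 2.011:

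| True difference (SD, assumed) | Noncentrality | Power | p > .05 |
|---|---|---|---|
| 0.3 | 1.06 | 18% | 82% |
| 0.5 | 1.77 | 41% | 59% |
| 0.8 | 2.83 | 79% | 21% |

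Power of 80% needs a true difference of about 0.81 SD.

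*Precision.* The 95% interval half-width is 2.011·√(2/25) = 2.011 × 0.283 = 0.57 SD. For the healed proportion it is 1.96·√(2p(1−p)/25): 22 percentage points if 80% heal and 17 points if 90% heal (both rates assumed).

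*Equivalence.* Two one-sided tests at 5% (90% interval inside ±m), true difference 0, power by t-based simulation:

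| Margin m (SD, assumed) | Power at 25 per arm |
|---|---|
| 0.5 | 10% |
| 0.6 | 34% |
| 0.8 | 75% |
| about 0.84 | 80% |

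The last row lies between simulated values of 79% at 0.83 SD and 81% at 0.85 SD. A known-SD check at m = 0.5 agrees: 2Φ(0.5/0.283 − 1.645) − 1 = 2Φ(0.123) − 1 ≈ 0.10.

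*Fewer complete cases.* The statistics section analyses only complete follow-up. With an assumed 20 complete cases per arm, p > .05 at 0.5 SD rises to 66%, and equivalence power falls to 3% at a 0.5 SD margin and 60% at 0.8 SD.

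**The case against.** The best defence has four parts.

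- **No rule equates p > .05 with equality.** A reader might infer that the analysis will declare the implants equal whenever p > .05. The article does not say so: it attaches a conclusion only to p ≤ .05. The Discussion's hope of showing comparability makes the misreading a real risk, but it remains a risk and not a written decision rule. This part stands.
- **The final details are left to a statistical analysis plan.** That plan is not shown and could contain a margin or an interval rule. The absent margin is therefore not a fault in its own right, and the conclusion must be confined to tests named in the article. The deferral does not cure the conflict, because the hypotheses and the tests are both already stated and they disagree.
- **This is a pilot with unknown effects, and the article says so.** That excuses the lack of a formal sample size. It also counters the inference that the trial cannot answer its question at all, since comparison and hypothesis generation are stated objectives too. Nor is it right that 25 per arm could never show equivalence: that depends on the margin. Likewise, p > .05 is not likely at every relevant difference; at 0.8 SD it occurs in 21% of trials. Pilot status does not excuse hypotheses that run opposite to their tests.
- **The varying phrases are only expectations.** The equivalent-or-better and same-outcome statements sit in the abstract, Background and Discussion, and only one section lists what will be tested. They do not redefine H1. They do weaken the suggestion that H0 and H1 were simply swapped by accident, since sameness is a recurring aim.

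**Conclusion.** The point holds as a contradiction between two parts of the article. The stated H0 and H1 are the reverse of those belonging to the named tests, no test named in the article can establish H1, and nothing else in the article resolves this. That conclusion is logical and needs no assumed effect size.

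The figures show only how serious a misreading could be. They rest on 25 analysed per arm, two-sided 5% testing, normal data, and assumed differences and margins in SD units. On that basis a non-significant result would leave differences of about half an SD either way compatible with the data when the estimate is near zero. Because the conflict affects the trial's central inference and is cheap to remove, it should be corrected before any comparison by arm.

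**What to change.** Make Objectives and hypotheses agree with the statistics section:

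1. Restate H0 as no difference between the arms and H1 as a difference, matching the planned tests.
2. Report the between-group difference with its 95% confidence interval as the main result for MRI healing, ankle range of motion and maximum ankle power.
3. State that p > .05 will not be reported as equal, equivalent or comparable unless the 90% interval (two one-sided tests at 5%) lies within a margin fixed before any comparison by arm.

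If the sponsor prefers to keep the equivalence aim, the margin and interval rule must replace the difference test as the test of H1. The sponsor should then accept what 25 per arm can support. By 2·((1.645 + 1.282)/m)², 80% power with identical arms needs 69 per arm at an assumed margin of 0.5 SD and 27 at 0.8 SD.

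The statements of expectation in the abstract, Background and Discussion should be brought into line with whichever option is chosen.

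Cost: neither option requires more patients or data. Because the trial is registered, ethics-approved and already recruiting, restating its hypotheses may need a protocol or analysis-plan amendment. Under the first option the trial gives up a claim of equality, which the named tests could not have supported.
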